## Methods

### Study design

This single-blind (assessor blinding), three-arm, superiority RCT will include 3 evaluation sessions (baseline, the end of interventions (6 weeks) and the end of follow-up (3 months)), and 6-week interventions for three groups (CRTs, RT and RTFE). The flow chart of this study is shown in Fig. 1. The SPIRIT figure is shown in Fig. 2.

**Fig. 1 Fig1:**
[figure not shown]
Flow chart of this trial

**Fig. 2 Fig2:**
[figure not shown]
Example template of recommended content for the schedule of enrolment, interventions, and assessments*. − *t*_1_, enrolment week 0; *t*_0_, allocation and baseline week 0; CRTs, conventional rehabilitation therapies; RT, robot-assisted training; RTFE, robot-assisted training combined with functional electrical stimulation; FMA-UE, Fugl-Meyer Assessment of Upper Extremity; MBI, modified Barthel Index; VAS, visual analogue pain scale

This study will be conducted between 1st September 2023 and 1st March 2024 in the rehabilitation centre of West China Hospital of Sichuan University, Chengdu, Sichuan Province, China.

### Eligibility criteria

Participants presenting in this trial will be recruited based on the following criteria:

#### Inclusion criteria

Aged 18 to 80Clinical diagnosis of stroke (cerebral infarction, primary intracerebral haemorrhage, subarachnoid haemorrhage, etc.)Between 1 week and 1 year since the first onset of strokeUpper limb, functional limitation: the score of Fugl-Meyer Assessment of Upper Extremity (FMA-UE) ≥ 11 and ≤ 33All of the following muscle strengths assessed by manual muscle test (shoulder flexion/extension, shoulder abduction/adduction, elbow extension/flexion, wrist flexion/extension) ≤ 3Sufficient to offer consent to take part in this study and able to follow the requirements of the protocol

#### Exclusion criteria

The history of more than one strokeOther current significant upper extremity impairment, e.g., frozen shoulder, fracturePrevious any kinds of robot-assisted rehabilitation experienceEnrolment in another clinical trialAccepted upper limb botox injection, isokinetic training, and electrotherapy within 3 months

#### Discontinuing criteria

Withdrawing will be in consideration if:Participants decide to withdrawParticipants develop serious diseases such as serious heart attacks and strokeTherapists, stroke physicians and investigators may also withdraw participants if they think this trial is no longer in patients’ interest; for example, continuing this trial might induce more adverse events

### Sample size

The sample size is 60 subjects (20 subjects in each group). As we did not retrieve an appropriate study, according to Cohen’s theory [17], the effect size of 0.25 was applied. G*Power was used to estimate the sample size (repeated measures analysis of variance (ANOVA), within-between interaction) with effect size = 0.25, *α* = 0.05, 1 − β = 0.95, and the number of groups = 3. The total sample size based on the result was 54 (18 subjects per group). Considering 10% attrition, we inflated the total sample size to 60.

## Interventions

There will be three groups (RTFE group, RT group, and CRTs group) in this study. Participants in the CRT group will receive only conventional rehabilitation therapies. Participants in the RT group will receive robotic training with CRTs and a sham FES. Participants in the RTFE group will receive robotic training with FES and CRTs. The duration of CRTs in each group will be the same, and RT in both the RT group and the RTFE group will be set based on the same method in the Appendix.

During this experiment, all participants will be required to maintain the original lifestyle and try not to seek for other upper limb-related medical care such as extra kinesitherapy, which is for reducing the impact of adjusting lifestyle or different amounts of training.

### CRT group (conventional rehabilitation therapies group)

Eligible participants in the CRTs group will be treated with daily rehabilitative training and clinical pharmacotherapy. All training will be set based on the participants' functional situation and aim to develop upper limb function. The rehabilitative training mainly includes functional training, manual training, coordination training, mental practice and task-oriented training. Additionally, all therapists will be required to track and record all specific rehabilitation programmes with detailed information such as duration and frequency. Standard CRTs will be conducted for 45 min per session, one session per day, 5 days per week, for 6 weeks.

### RT group (robot-assisted training group)

Participants in the RT group will receive both RT and CRTs. The Upper Limb Training and Evaluation System (A6) which is produced by Guangzhou Yikang Medical Equipment Industrial Co., LTD, used in the RT programme consists of an exoskeleton with 3 modules (shoulder module, elbow module, and wrist module), a laptop and a screen. It will support hemiplegic individuals to perform passive, partially active, and totally active upper limb movements of shoulder flexion/extension, shoulder abduction/adduction, elbow flexion/extension, and wrist flexion/extension. This machine could also provide simulating ADL tasks such as drinking, feeding, and combing hair with different levels of assistance. The screen provides visual and audio feedback by showing a virtual character doing the same action with users, and sounding if a particular movement is successfully performed. Specifically trained occupational therapists will choose an individualized RT training plan consisting of several motions for each participant based on his/her functional status. The process of making the RT programme has been shown in the Appendix. Participants in the RT group will receive sham FES. For the sham stimulation, the stimulator will be turned on but the intensity button will be set to 0; thus, there will be no output. Participants in the RT group will be notified that the stimulation will have been set below the sensory threshold. Participants will receive RT training for 45 min per session, one session per day, 5 sessions per week, for 6 weeks. Participants in the RT group will also receive the CRTs as same as in the CRT group.

### RTFE group (robot-assisted training combined with functional electrical stimulation group)

Participants in the RTFE group will receive CRTs and RTFE. Both CRTs and RT will be as same as those in the RT group. Extra FES will be set on people in the RTFE group. FES (Dualpex-071 Quark Medical, Brazil) will be applied during the RT for 45 min by the surface electrodes. The position of surface electrodes will be set on the surface of muscle involved in the RT movement, which primarily includes the deltoid, triceps brachii, biceps brachii, wrist flexor and wrist extensor muscle of the paretic arm. Stimulation parameters will be set with (1) frequency = 40 Hz, (2) pulse width = 300 μs, (3) on time (contraction = 8 s), (4) off time = 2 × on time, and (5) current intensity = the maximum tolerance of participant. These parameters have been set considering a previous study showing a positive change in reaching motor performance in stroke survivors [18]. The FES will be given synchronously with robot movement. The intensity of FES will be set to the maximum which can be tolerated by participants. FES will be conducted simultaneously when the RTFE participants accept the RT.

## Outcomes

### Primary outcome

#### FMA-UE (Fugl-Meyer Assessment of Upper Extremity)

The primary outcome of this study is the upper limb neuromuscular function measured by FMA-UE at the end of week 6. FMA-UE is an assessment of the upper extremity in terms of neuromuscular function with high intra- and inter-reliability and concurrent validity [19, 20]. This scale consists of 33 items, which mainly focus on the reflex activity, volitional movement and functional movement of the upper extremity, wrist and hand, with the score of each item ranging from 0 to 2 (0 = no performance at all; 1 = partial performance; 2 = full performance). The maximum score for this assessment is 66 and the minimal clinically important differences are 12.4 (upper extremity), 5.6 (upper arm), and 4.9 (wrist/hand) [21]. A higher FMA-UE score means better performance in neuromuscular function.

### Secondary outcomes

The secondary outcomes include ADL measured by the modified Barthel index (MBI), upper limb pain intensity assessed by the visual analogue scale (VAS), and quality of life assessed by EuroQol 5-Dimension 5-Level (EQ-5D-5L).

#### MBI (modified Barthel Index)

ADL will be assessed by the MBI, which has shown good validity, reliability and sensitivity in Chinese stroke patients’ ADL assessment [22]. MBI is a functional scale consisting of 10 items including feeding, bowel control, bladder control, personal hygiene, transfer, dressing, toilet ambulation, bathing and stairing, and each item in MBI is categorized into 5 levels. The final score of MBI ranges from 0 to 100, of which a higher score indicates a better capacity of independence.

#### VAS (visual analogue scale)

The upper limb pain intensity in our study will be captured by a 0–10 visual analogue pain scale. According to their severity of pain, participants will be required to mark on a 100-mm line. The far left of the line represents no pain and the far right means the worst possible pain. The score of VAS will be represented as the number corresponding to the marked position. VAS shows good intra- and inter-reliability and validity across many experiments and different populations [23].

#### EQ-5D-5L (EuroQol 5-Dimension 5-Level)

Quality of life will be assessed by EQ-5D-5L. EQ-5D-5L is a measurement of quality of life based on 5 items of mobility, self-care, usual activities, pain/discomfort, and anxiety/depression. The score of EQ-5D-5L is between 0 (dead) to 1 (the best quality of life). Its reliability and validity in stroke patients have been discussed in previous articles [24–26].

Demographic details will be collected. These will include (1) age, (2) sex, (3) diagnosis: ischemic stroke or hemorrhagic stroke, (4) time of the first onset of stroke, (5) the side of the affected arm, and (6) Brunnstrom stage.

## Statistical methods

Normally distributed variables will be presented by means with standard deviations, and nonnormally distributed data will be presented by medians with interquartile ranges. Categorical variables will be presented by proportion and frequency.

Investigators in charge of the result analysis will be blinded to the group allocation. All data will be analysed by Statistical Package for the Social Science (SPSS) version 26.0 software. The score of the primary outcome and secondary outcomes will be measured at different time points for the same subject. Two-factor repeated-measures analysis of variance (ANOVA) will be used for the statistical analysis for all outcomes with the sphericity test before analysis. If the data is dissatisfied with the sphericity test, the Green-house-Geisser method will be used to correct it. Simple effects tests will be used for the further exploration of interaction effects by time and group. Scheirer-Ray-Hare test will be used if the data are not satisfied with normal distribution. The statistical difference will be set at a *P* value less than 0.05.

The subgroup analysis will be conducted for further exploration. The comparison will be conducted between people with the first stroke onset for less than three months and residual people in terms of the score of FMA-UE. We will test whether RTFE shows the same effectiveness in people with different durations after first stroke onset by two-factor repeated measures ANOVA with the same statistical difference.

All analyses in this trial will follow the intention-to-treat principle. Based on this principle, all participants no matter what kind of intervention they received will be regarded as randomized. Multiple imputations based on 5 replications and the Markov-chain Monte Carlo method in the SAS MI procedure will be used to handle the missing data.

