## Abstract

**Introduction:**

About 17–80% stroke survivors experience the deficit of upper limb function, which strongly influences their independence and quality of life. Robot-assisted training and functional electrical stimulation are commonly used interventions in the rehabilitation of hemiplegia upper extremities, while the effect of their combination remains unclear. The aim of this trial is to explore the effect of robot-assisted upper limb training combined with functional electrical stimulation, in terms of neuromuscular rehabilitation, compared with robot-assisted upper limb training alone.

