**Discussion:**

We expect this three-arm randomized controlled trial to explore the effectiveness of robot-assisted training combined with functional electrical stimulation in improving post-stroke upper limb function compared with robot-assisted training alone.

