## Objective and hypothesis

The primary objective of this study is to investigate the effectiveness of RTFE on the upper extremity neuromuscular function in stroke patients. The null hypothesis is that there is no difference among participants who receive RTFE, RT and CRTs in terms of upper limb neuromuscular function development. The secondary objective is to investigate whether RTFE is superior to RT with respect to improving the ability of ADL, quality of life and reducing post-stroke pain.

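### The primary analysis is a three-arm, three-visit interaction test that fits the three-group null but isolates neither week 6 nor RTFE versus RT, which the protocol elsewhere makes its question

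*Protocol article*

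**What the plan says.** **Endpoint.** Primary outcome: "The primary outcome of this study is the upper limb neuromuscular function measured by FMA-UE at the end of week 6". This is one scale at one visit.

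**Comparison, as the Abstract has it.** The aim is the effect of the combination "in terms of neuromuscular rehabilitation, compared with robot-assisted upper limb training alone". The Abstract's Discussion repeats it: "in improving post-stroke upper limb function compared with robot-assisted training alone". The Discussion in the body names RTFE against RT alone too, but also mentions a comparison among all three groups.

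**Comparison, as Objective and hypothesis has it.** "The null hypothesis is that there is no difference among participants who receive RTFE, RT and CRTs". No pair and no visit is named. RTFE against RT appears there only one sentence later, for other outcomes: "The secondary objective is to investigate whether RTFE is superior to RT with respect to improving the ability of ADL", with quality of life and pain.

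**Analysis.** Under Statistical methods, a two-factor repeated-measures ANOVA "will be used for the statistical analysis for all outcomes with the sphericity test before analysis". Study design gives three arms and three visits (baseline, 6 weeks, 3 months). Then: "Simple effects tests will be used for the further exploration of interaction effects by time and group". The only threshold given is P below 0.05.

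**Sample size.** G*Power, within-between interaction, effect size 0.25, alpha 0.05, power 0.95, three groups: 54 in total (18 per group), raised to 60 for 10% attrition.

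**The concern.** The endpoint, the aim, the null hypothesis and the test do not describe one question. The interaction has (3 − 1)(3 − 1) = 4 degrees of freedom and responds to any arm difference in the course over time: any pair, any visit. RTFE versus RT at week 6 is reached only through follow-up tests described as exploration.

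This matters here because of the design. Under Interventions, both robot arms receive the same conventional therapy as the CRT arm plus a 45-minute robot session, five times a week for six weeks. A difference between CRT and the robot arms that has nothing to do with FES is therefore plausible. The Introduction cites equivalence of RT and CRTs, but here RT is added to CRTs, not substituted for them. A significant main analysis could thus leave the FES question open. Conversely, a true RTFE-RT difference at week 6 could be missed if the interaction has to be significant first. The 95% power could also be read as applying to a comparison for which it was never calculated.

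**Working it through.** **1. Reproducing the plan's figure.** Inputs from Sample size and Study design: f = 0.25, alpha = 0.05, k = 3 groups, m = 3 visits. Assumed, because not stated: between-visit correlation ρ = 0.5 and sphericity (ε = 1).

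- λ = f²·N·m/(1 − ρ); df1 = (k − 1)(m − 1); df2 = (N − k)(m − 1).
- N = 54: λ = 0.0625 × 54 × 3/0.5 = 20.25; df = 4 and 102; power 0.958.
- N = 51: λ = 19.125; df = 4 and 96; power 0.946.

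So 54 is the smallest multiple of 3 that reaches 0.95, and 54/0.9 = 60. The arithmetic is right, and it is the power of the 4-df interaction.

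**2. What f = 0.25 implies for RTFE versus RT.** Take equal arms at baseline and the same shift at both later visits. The visit pattern (0, 1, 1) has variance 2/9. The interaction f is then the square root of (variance of the arm shifts × 2/9), in SD units.

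- RT and RTFE both d above CRT: the arm variance is d² × 2/9, so f = d × 2/9. f = 0.25 gives d = 1.125, with an RTFE-RT difference of **zero**.
- Arms evenly spaced by 0.65 SD: the arm variance is (2/3) × 0.65² = 0.282, so f = √(0.282 × 0.222) = 0.25, with an RTFE-RT difference of **0.65 SD**.

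The effect size used for sizing is compatible with no FES effect at all.

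**3. How often the interaction is significant without an FES effect at week 6.** Simulated trials, SD 1, compound symmetry with ρ = 0.5.

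| Scenario | Per arm | Interaction significant |
|---|---|---|
| RT = RTFE, both 0.5 SD above CRT | 18 | 30% |
| RT = RTFE, both 0.8 SD above CRT | 18 | 69% |
| RT = RTFE, both 1.125 SD above CRT | 18 | 96% |
| RTFE gains 0.5 SD at month 3 only | 20 | 34% |
| RTFE gains 0.8 SD at month 3 only | 20 | 75% |

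With ρ from 0.3 to 0.7 and 20 per arm, the first pattern gives 24–54% at 0.5 SD and 60–95% at 0.8 SD.

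**4. Error of the RTFE-RT test itself.** In the 1.125 SD scenario, RTFE versus RT at week 6 after a significant interaction is significant in about 5% of trials, which is nominal. If a significant RTFE-RT difference at month 3 may also support the claim, the rate is about 9%.

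**5. Power for RTFE versus RT at week 6 (18 per arm, ρ = 0.5).**

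| Scenario | Test | Direct | After a significant interaction |
|---|---|---|---|
| Even spacing, 0.65 SD | t test | 48% | 46% |
| Only RTFE differs, 0.8 SD | t test | 64% | 48% |
| Only RTFE differs, 0.8 SD | ANCOVA | 77% | 60% |

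The ANCOVA adjusts for baseline FMA-UE with residual variance pooled over three arms. Simulated figures here agree across runs to about one percentage point.

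**6. Size of difference the contrast can detect.** A two-sided t test at 0.05 with 20 per arm has 34% power at 0.5 SD and 69% at 0.8 SD. It needs 0.91 SD for 80% power and 1.17 SD for 95%. The protocol gives no SD and no between-arm difference, so these stay in SD units.

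**The case against.** The strongest reply is that the protocol is coherent on its own terms. The null under the primary objective is explicitly three-group, the interaction tests it, and the sample size was computed for that interaction. This stands: the analysis does match Objective and hypothesis. What remains is that this section disagrees with the Abstract's aim, names no visit, and attaches RTFE-versus-RT superiority to the secondary outcomes only.

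A second reply is that simple effects tests can compare the arms at week 6. They can, and at that visit their error is nominal. But they are presented as exploration of an interaction, so the contrast that the Abstract calls the aim has no confirmatory standing.

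A third is that an unseen SAP may settle contrasts and multiplicity. Silence on adjustment of the simple effects is indeed no finding. The choice of test and the basis of the sample size, however, are fixed in the protocol.

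Three stronger readings are tempting and are not supported:

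- A reader might infer that the trial will declare FES effective on a significant interaction. No such rule is written; an omnibus test that rejects because one arm differs is doing its job.
- A reader might infer an inflated false-positive rate for the FES claim. The roughly 9% arises only if month 3 counts as a second route, and the primary outcome is fixed at week 6.
- A reader might infer that requiring the interaction always costs much power. Under even spacing it costs about 2 points. In that scenario most of the gain from a direct ANCOVA (about 59%, against 48% for the t test) comes from baseline adjustment, not from dropping the interaction requirement.

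**Conclusion.** The point holds as a mismatch between question and analysis. The Abstract's aim and the week-6 endpoint are not tied to the test that is planned and sized; the three-group null is. The mismatch follows from the text and needs no assumption.

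Its size does rest on assumptions: 18 per arm, ρ = 0.5, compound symmetry, and the chosen mean patterns. On these, the main test is significant in about 96% of trials with no FES effect when both robot arms exceed CRT by 1.125 SD. Making RTFE versus RT conditional on it costs between about 2 and 17 points of power, depending on the pattern. The 95% power statement is correct for the interaction and does not carry over to RTFE versus RT at week 6. Because this decides what the trial may conclude about FES, it should be settled before data are analysed.

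**What to change.** - Reconcile the Abstract (aim and Discussion), Objective and hypothesis, Sample size, Primary outcome and Statistical methods so that all name the same primary comparison and visit.
- Name one primary test: the baseline-adjusted RTFE minus RT difference in FMA-UE at week 6, from ANCOVA or the week-6 contrast of a mixed model for repeated measures. Test it two-sided at 0.05 with a 95% CI, and do not make it conditional on the interaction.
- Reword the primary null hypothesis to RTFE versus RT at week 6.
- Make the three-arm interaction, the contrasts with CRT and the month-3 visit secondary.
- State in Sample size that the 95% power refers to the interaction, and give the power of the primary contrast for stated differences.

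The cost is wording; no new data or visits are needed. The price is that comparisons with CRT become secondary, and that the power for the primary contrast is openly below 95% unless the true difference is large. Without baseline adjustment, 20 per arm reach 95% only at about 1.17 SD.

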## Data collection and management

### Data collection and storage

Outcomes will be measured by two certified, well-experienced occupational therapists who will neither be informed of the allocation nor participant in any interventions. The participants will receive assessments of the FMA-UE, MBI, VAS and EQ-5D-5L at baseline, after completion of their interventions (6 weeks), and at the end of follow-up (3 months). Case report forms (CRFs) will be used to record participants’ clinical information. The corresponding questionnaires will be used to record the results of the assessment. These paper-based data will be transferred into Microsoft Excel 2020 and EpiData 3.1 software for good management. Two independent researchers will take charge of double data entry and verification to guarantee the accuracy and truthfulness of the data. The original data will be checked again for further verification if there is inconsistent data inputting or missing. All data will not be allowed to be modified after input and check.

Personal data will be strictly confidential. The original paper CRFs of participants will be locked in a file cabinet at the research site. Coded ID numbers will be used in all reports, data collection, processing and administrative forms for keeping participants’ confidentiality. All paper records with names or personal identifiers will be stored separately from documents with a coded number. The data will be stored in a computer with passwords set by the leader of this project at the research site, and only staff involved in this study will be allowed to access it. The personal information of participants will not be released without the written permission of the participant.

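### The fallback for non-normal data, the Scheirer-Ray-Hare test, has no patient term, yet it replaces a repeated-measures analysis of three visits per patient

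*Protocol article*

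**What the plan says.** The Statistical methods section states the data structure plainly: "The score of the primary outcome and secondary outcomes will be measured at different time points for the same subject". The main analysis respects it: "Two-factor repeated-measures analysis of variance (ANOVA) will be used for the statistical analysis for all outcomes with the sphericity test before analysis", with a Greenhouse-Geisser correction if sphericity fails. The group by time interaction is then followed up: "Simple effects tests will be used for the further exploration of interaction effects by time and group". The significance rule is "The statistical difference will be set at a *P* value less than 0.05".

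The same paragraph gives the alternative for non-normal data: "Scheirer-Ray-Hare test will be used if the data are not satisfied with normal distribution". The Methods part of the Abstract says the same. Neither place limits the test to one visit or to change scores, or adds a patient term. As a two-factor test named directly after the two-factor ANOVA, it can only be read as its replacement, for the primary outcome as well as the secondary ones.

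The Sample size section powers the within-between interaction of a repeated-measures ANOVA with "effect size = 0.25, *α* = 0.05, 1 − β = 0.95, and the number of groups = 3". This gives 54 patients, raised to 60 for 10% attrition. The visits are baseline, 6 weeks and 3 months.

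**The concern.** The Scheirer-Ray-Hare test extends Kruskal-Wallis to two factors. It ranks all values together, here 60 × 3 = 180 with complete data, and treats each as a separate independent unit. It has no term for the patient, although the paragraph that names it says the scores come from the same patients.

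Ignoring the correlation does harm in two directions. The group comparison is made between patients, so treating three correlated scores as three patients makes it too liberal. Time and group by time are compared within patients, so leaving the stable differences between patients in the error term makes those tests too conservative. The trial could report a false group effect, or miss the interaction it was sized to detect.

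**Working it through.** **The plan's own figure.** Inputs from the Sample size section: f = 0.25, α = 0.05, power 0.95, k = 3 groups. From the visit schedule: m = 3. Assumed, because not stated: within-patient correlation ρ = 0.5 and sphericity (ε = 1). For the within-between interaction:

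- λ = f² × N × m / (1 − ρ) = 0.0625 × 54 × 3 / 0.5 = 20.25
- df1 = (k − 1)(m − 1) = 4; df2 = (N − k)(m − 1) = 51 × 2 = 102
- Power is 0.958 at N = 54 and 0.946 at N = 51, so 54 reproduces. Then 54 / 0.9 = 60.

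With ρ = 0, the value at which Scheirer-Ray-Hare would be valid, the same calculation needs N = 102. So 54 is reached only by counting on correlated visits.

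**Why the test errs both ways.** The statistic is H = SS(effect) / MS(total) on the pooled ranks. It is referred to chi-square with 2 df for group, 2 for time and 4 for the interaction. With equal correlation ρ between visits and no true effects, the mean square for group is about (1 + 2ρ) times MS(total), and that for the interaction about (1 − ρ) times.

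- Group: the null rejection rate is about 0.05^(1/(1 + 2ρ)). This gives 0.05^(1/1.6) = 15% at ρ = 0.3, 0.05^(1/2) = 22% at ρ = 0.5, and 0.05^(1/2.6) = 32% at ρ = 0.8.
- Interaction: the rate is about P(χ²₄ > 9.488 / (1 − ρ)), which is 0.9% at ρ = 0.3 and 0.08% at ρ = 0.5.

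**Simulation under the null** (10,000 trials per setting, 18 or 20 per arm, 3 visits, normal and log-normal data, range over these settings):

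| ρ (assumed) | Group, no common time effect | Group, 0.8 SD common time effect | Group by time, no common time effect |
|---|---|---|---|
| 0 | about 5% | about 3% | about 5% |
| 0.3 | 15–16% | 11–12% | about 1% |
| 0.5 | 21–22% | 17–18% | 0.1–0.2% |
| 0.7 | 27–29% | 23–24% | 0.01% or less |
| 0.8 | 31–32% | 26–27% | 0% |

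The test holds its level at ρ = 0, so the departures come from the correlation. Further runs at 20 per arm over ρ = 0.3 to 0.8 gave 14–33% for group with no common time effect and 6–16% with one of 1.5 SD. A common time effect enlarges MS(total), which reduces the group inflation.

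**Interaction power** at f = 0.25, ρ = 0.5 and 18 per arm, over several interaction patterns:

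| Recovery common to all arms (assumed) | Scheirer-Ray-Hare | Repeated-measures ANOVA |
|---|---|---|
| none | about 45–63% | about 95–96% |
| 0.8 SD | about 42% | about 95–96% |
| 1.5 SD | about 5–25% | about 95–96% |

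With 20 per arm and no common recovery, one pattern gave 69% against 97%.

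**Keeping the patient in the analysis.** A repeated-measures F test on the same pooled ranks (log-normal data, ρ = 0.3 to 0.8, 18 or 20 per arm) had null rejection of about 0.048–0.054 for group and 0.048–0.058 for the interaction. At f = 0.25 and ρ = 0.5 its interaction power was 0.94 (18 per arm) and 0.96 (20 per arm). The fault therefore lies in dropping the patient, not in using ranks.

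**The case against.** The strongest reply is that this is only a fallback. The main ANOVA is unaffected, and nothing in the document shows that normality will fail. For FMA-UE that is fair: the restriction to 11–33 applies at entry, while later scores can run up to 66. A reader might infer from the entry range that the fallback will probably decide the primary outcome, but the document does not establish that. The argument is stronger for pain VAS, which is bounded at zero, and for EQ-5D-5L, described as running from 0 to 1.

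A second reply is that the powered effect is the interaction, where the test is conservative. This also stands in part. A reader might conclude that none of the fallback's p-values could be used. That goes too far: a test that rejects a true null about 1% of the time or less does not produce spurious interactions. The false-positive risk belongs to the group main effect, which averages over baseline and is not the powered contrast.

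Third, a reader might infer that the interaction test has almost no power. The very low values need a common recovery of about 1.5 SD, and the Sample size section states no time effect. Enrolment from 1 week after stroke makes substantial shared recovery plausible, but its size is an assumption. The two harms also do not peak together, because a larger common time effect lowers both interaction power and the group inflation.

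None of these replies makes a test for independent observations suitable for three visits per patient. Nor is this a detail left to an analysis plan that is not shown: the article names the test, twice.

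**Conclusion.** The fallback is wrong as written, because it contradicts the data structure described in its own paragraph. If it is triggered, a significant group effect cannot be trusted, a non-significant interaction says little, and a significant interaction would remain credible.

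The sizes rest on an assumed correlation of 0.3 to 0.8, equal between all pairs of visits. The group test then rejects a true null about 14–33% of the time with no common time effect and about 6–16% with one of 1.5 SD. The power loss, from about 95% to 45–63% or to 5–25%, further assumes f = 0.25, correlation 0.5, 18 per arm, and respectively no common recovery or 1.5 SD of it. The direction of both errors needs only positive within-patient correlation, on which the sample size itself relies. The point does not extend to the main ANOVA.

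**What to change.** Delete the Scheirer-Ray-Hare test from the Abstract and from Statistical methods, and name a fallback that keeps the patient as the unit. Two choices fit:

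- for group by time on any outcome, a rank-based longitudinal ANOVA-type statistic (Brunner-Langer F1-LD-F1);
- for FMA-UE at week 6, the stated primary outcome, rank ANCOVA adjusting for baseline.

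State which one applies to which outcome.

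The cost is wording in two places, with no change to sample size, visits or data collection. The drawback is that the procedure may have to be run outside SPSS; the plan already goes outside SPSS for imputation, which uses the SAS MI procedure. Whether to keep a normality-triggered switch at all, or to replace the main ANOVA, is a separate question that this defect does not settle.
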